### Trial design {8}

The design of this randomized clinical trial is a “waiting control group design”, which compares the immediate intervention group with the delayed intervention group. The latter one will serve as a control group. The intervention cannot be blinded, but the outcome measure (lung function tests) is blinded, because the technician does not know to which group (immediate or delayed intervention) the subject belongs to. Moreover, the absence of any intervention in subjects with gingivitis would be unethical, but an intervention delayed for 4 weeks seems acceptable.

## Methods: participants, interventions and outcomes

### Study setting {9}

This study will be executed in the academic outpatient dental clinic at the Ludwig-Maximilians-University of Munich.

### Eligibility criteria {10}

The study subjects should have an age between 18 and 30 years, because of the life period with peak achievements of lung function.

The following are the inclusion criteria:Non-smoking subjects with biofilm-induced gingivitisParticipants must be vaccinated against COVID-19Negative test result for COVID-19 before each dental visit (needs to be modified in adherence to current regulations)

The following are the exclusion criteria:Active smokingOther gingival/ periodontal diseases [8]Having at least one tooth with a periodontal pocket depth and attachment loss > 4 mmAsthma, diabetes and other chronic diseases, and anti-inflammatory treatment for chronic diseasesPregnancyLong COVID-19Not able/willing to provide informed consentNot available for the period of repeated examinations

The recruiting will start with the pre-selections of subjects with occasional gum bleeding. These subjects are screened for further eligibility for the intervention study. The continuous recruitment will address primarily patients of dental school and university students.

### Who will take informed consent? {26a}

The informed consent will be obtained by the recruiting dentists.

### Additional consent provisions for collection and use of participant data and biological specimens {26b}

On the consent form, participants will be asked if they agree to the use of their data should they choose to withdraw from the trial. Participants will also be asked for permission for the research team to share relevant data with people from the cooperating universities. This trial does not involve collecting biological specimens for storage.

### Interventions

#### Explanation for the choice of comparators {6b}

Safeguarding good and lifelong oral hygiene is a prerequisite for preserving dental and oral health. During the last decades, many associations between oral health—especially periodontal health—and general medical diseases, e.g. diabetes, cardiovascular diseases, adipositas/obesity, chronic kidney disease or chronic obstructive pulmonary diseases, have been described [7, 28, 29, 31, 43, 54]. Many studies followed a wide variety of scientific questions but mainly included older adult populations. Interestingly, there is limited information available for younger groups which may enter the initiation phase of both periodontal and general diseases. Available studies have shown that potential associations between periodontal health and potential risk factors became detectable also in young populations. Here, Pitchika et al. [46] have shown that elevated high-sensitivity C-reactive protein blood levels were positively associated with gingival health, smoking habits and overweight/obesity. On the basis of this finding, it can be concluded that other known associations in adults might be probable transferable to a younger age as well.

#### Intervention description {11a}

##### Intervention 1

The association between microbial dental biofilm and caries is known for decades [18, 32, 39]. Furthermore, there is clear evidence that the (non-)presence of dental biofilm triggers the initiation, persistence, progression or healing of dental biofilm-induced gingivitis which may be later progressed into periodontitis [8, 9, 32, 63]. Therefore, the daily control of the dental biofilm by each individual is essential over the lifetime and needs to be considered in clinical studies due to many reasons as well. In the present clinical study, oral hygiene instructions are needed to (1) provide the essential knowledge to safeguard dental well-being as best as possible which goes hand in hand with the scientific aim (2) to standardize the daily oral hygiene routines between all study subjects over the whole study period. Therefore, intensified oral hygiene instructions which are based on recently published evidence-based recommendations by the German Society of Dentistry [12] are part of the “intervention 1” phase and include the following preventive measures:

Motivational interviewing, individualized demonstration and instruction for optimal, systematic and regular oral hygiene using a vertical brushing technique (e.g. BASS technique).Recommendation to use fluoridated toothpaste (fluoride content 1000–1450 ppm).Instruction for using dental floss due to the fact that proximal niches cannot be cleaned by tooth brushing alone. Worthington et al. [67] concluded in their most recently published Cochrane review that the use of dental floss or interdental brushes in addition to tooth brushing may reduce gingivitis or plaque, or both.

To ensure an ongoing acceptance and the motivated use of basic oral hygiene measures, all participants will be repeatedly informed during the study visits about the benefits of simple and basic preventive measures.

##### Intervention 2

The professionally administered supra- and subgingival biofilm control goes hand-in-hand with the removal of periopathogens improves gingival inflammation [10] and is, therefore, an essential part of the 2nd intervention phase. This procedure includes the removal of calculus using hand instruments, e.g. scalers, and/or ultra-sonic instruments. In the second step, all teeth will be systematically cleaned using rotating toothbrushes with a low-abrasive polishing paste. In the last step, all teeth will be fluoridated using a varnish (Fluor Protector, Vivadent, Schaan, Lichtenstein). As pointed out before, each subject will be informed about their oral health status, and appropriate oral hygiene instructions will be provided by the professional dental team.

In addition to the professional tooth cleaning a full-mouth disinfection using a non-alcoholic, CHX-containing mouth rinse is included in the study protocol which has to be applied twice a day over a period of 14 days. Recent studies [3, 15, 49] showed short-term clinical benefits of one-stage full-mouth disinfection, when compared to the standard treatment strategy of consecutive tooth cleaning alone. Here, the mouth rinse may help to enable proper disinfection of the remaining intraoral niches which could not be reached by the dental instruments especially in patients suffering from periodontitis [50]. With respect to gingivitis patients, van Strydonck et al. [64] analysed the available literature in a systematic review and concluded that CHX mouth rinses together with oral hygiene instruction provided a significant reduction in plaque and gingivitis scores. In another more recently published Cochrane review by James et al. [23], the effectiveness of CHX mouth rinse used as an adjunct to mechanical oral hygiene procedures for the control of gingivitis was assessed in more detail. The authors concluded that there is high-quality evidence of a substantial, but short-term reduction in dental plaque formation when CHX mouth rinse was used as an adjunct to mechanical oral hygiene. In case of gingivitis, the data were insufficient to determine the reduction in gingivitis in association with CHX mouth rinse. Nevertheless, after 4 to 6 weeks of use, CHX mouth rinse reduced gingivitis by an odds ratio of 0.21 (95%CI 0.11 to 0.31) compared to placebo, control or no mouth rinse. There is no evidence that one concentration of CHX mouth rinse (0.1%/0.12%/0.2%) is more effective than another [23]. Nevertheless, the CHX effect on the biofilm is dose-dependent, and the optimum CHX dose is considered to be 20 mg twice daily [36] which represents an equivalent of 10 ml of 0.2% CHX mouth rinse [24]. A rinse time of 30 s appears to be effective and acceptable [24].

Rinsing with CHX mouth rinse for 4 weeks or longer may cause harmful extrinsic tooth staining. Therefore, all study subjects will have access to an additional tooth cleaning after finishing the study protocol.

#### Criteria for discontinuing or modifying allocated interventions {11b}

It is not planned to discontinue or modify the intervention for trial participants.

#### Strategies to improve adherence to interventions {11c}

A key issue in maintaining the adherence of study participants is to explain the importance of the trial, to illustrate the study protocol and why it is important to adhere to the scheduled appointments and the given oral hygiene recommendation consistently. Furthermore, the acceptance of basic oral hygiene measures in all participants will be ensured by remotivation. With respect to the short recall intervals, no phone checks were planned.

#### Relevant concomitant care permitted or prohibited during the trial {11d}

There are no restrictions regarding concomitant medical or dental care during study participation.

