#### Concealment mechanism {16b}

In principle, all participants will receive the same preventive measures owing to ethical reasons. Following the allocation of all subjects to one of the intervention groups, each participant will be informed by telephone about the appointment for the phase 2 baseline examination. As the protocol for the two groups—immediate and delayed intervention—cannot be blinded for the study team and participants, no efforts will be made to conceal this information.

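### Unrestricted dental care lets waiting controls have the trial's cleaning or CHX rinse elsewhere before the comparison, which would dilute the only randomised contrast

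*Protocol article*

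**What the plan says.** The rule on concomitant care (item {11d}) is one sentence: "There are no restrictions regarding concomitant medical or dental care during study participation".

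Trial design {8} describes a waiting-control trial that "compares the immediate intervention group with the delayed intervention group. The latter one will serve as a control group". The article justifies withholding treatment in the control arm on the ground that "an intervention delayed for 4 weeks seems acceptable".

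Intervention description {11a} sets out what is delayed. One component is "The professionally administered supra- and subgingival biofilm control", that is, scaling, polishing and fluoride varnish. The other is a rinse: a "CHX-containing mouth rinse is included in the study protocol which has to be applied twice a day over a period of 14 days".

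Concealment mechanism {16b} adds two relevant facts. Controls eventually get the same treatment: "In principle, all participants will receive the same preventive measures owing to ethical reasons". Participants also know their arm, because the protocol "cannot be blinded for the study team and participants, no efforts will be made to conceal this information".

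**The concern.** The two arms differ in one respect only: during the wait, controls have not yet had the cleaning and the CHX course. Both components are available outside the trial. A rule that allows all dental care therefore allows controls to receive the experimental treatment before the comparison, without any deviation being registered.

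Some such use is plausible. Eligibility criteria {10} pre-selects people with occasional gum bleeding and recruits mainly dental-school patients and students. Participants receive hygiene instruction and repeated motivation, and those in the delayed arm know they are waiting.

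If the intervention works, early receipt by controls pulls the between-arm FVC difference towards zero. A null result could then mean that gingivitis reduction does not affect lung function, or that some controls were already treated. The Objectives {7} want lung-function changes read as consequences of changed oral inflammation, so this ambiguity bears on the main question.

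**Working it through.** **Does any other text narrow the rule?**

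- Eligibility criteria {10}: no exclusion for outside cleaning or antiseptic rinses.
- Intervention description {11a}, Intervention 1: standardises daily hygiene across participants, but lists brushing technique, fluoride toothpaste and floss. It bars neither rinses nor professional cleaning elsewhere.
- Adherence strategies {11c}: covers appointments and hygiene recommendations.
- Non-adherence {20c}: does not apply, because permitted care is not non-adherence.

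None of these limits item {11d}.

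**Inputs from Sample size {14}.** Expected changes are m1 = 2 and m2 = 1, so the difference is 1. Variance is 1.5 per assessment, so the variance of the pre-post change is 3 (SD √3 = 1.732, given as about 1.7). The test is two-sided at 5% with 90% power, and about 60 per group are planned.

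**Reproducing the stated size.** n per group = 2 × SD² × (1.960 + 1.282)² / 1².

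- SD 1.7: 2 × 2.89 × 10.51 = 60.7, so 61, the stated figure.
- SD √3 unrounded: 2 × 3 × 10.51 = 63.0, so 64 after rounding up.

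The calculations below use the unrounded SD.

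**Dilution model.** Let c be the share of controls who obtain the intervention early, and f the share of the effect each receives. The expected control change is 1 + c·f, so the expected difference is

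d = 2 − (1 + c·f) = 1 − c·f.

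The standard error is √3 × √(2/60) = √0.1 = 0.316, and

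power = Φ(d / 0.316 − 1.96).

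| c | f = 1: d | f = 1: power | f = 0.5: d | f = 0.5: power |
|---|---|---|---|---|
| 0% | 1.00 | 88.5% | 1.000 | 88.5% |
| 5% | 0.95 | 85.2% | 0.975 | 86.9% |
| 10% | 0.90 | 81.2% | 0.950 | 85.2% |
| 20% | 0.80 | 71.6% | 0.900 | 81.2% |

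**Break-even for 80% power.** The difference must be at least (1.960 + 0.842) × 0.316 = 0.886, so c·f may not exceed 0.114. That is about 11% of controls at full effect, or 0.114 / 0.5 = about 23% at half effect.

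**Sample size needed for 90% power at f = 1.** 64, 70, 78 and 99 per group at c = 0, 5, 10 and 20%.

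**The article's less favourable variance.** With variance 2 per assessment (SD of change 2), power at 60 per group is 78.2% with no contamination, 69.3% at c = 10% and 59.1% at c = 20%, all at f = 1.

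Every value of c, and f = 0.5, is an assumption. The article gives no figure for either.

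**The case against.** - **The rule can be read more narrowly.** Concomitant care may mean care alongside the allocated treatment, with the timing of cleaning and CHX fixed elsewhere. That reading is possible, but nothing in the text states it. A control or an outside dentist applying the sentence as written would see no restriction.
- **Intervention 1 standardises hygiene routines**, so a self-bought rinse arguably departs from them. This has some force for rinses, although the listed measures do not mention them. It has none for professional cleaning elsewhere.
- **The rate is unknown and may be small.** The wait is about 4 weeks, controls are promised the same measures afterwards, and staff explain why adherence matters. This stands, and it limits how strongly the point can be pressed.
- **Full effect is an upper bound.** A contaminated control would need the equivalent of the cleaning plus the CHX course, early enough for FVC to respond. This also stands. In the half-effect case, power stays above 80% up to 20% contamination.
- **The planning already allows control improvement (m2 = 1).** Sample size {14} attributes that change to the control treatment, not to outside use of the trial intervention, so the allowance does not cover it.
- **Dilution cannot create a false positive, and unrestricted usual care is a legitimate design.** The first part is true. The second suits a trial of treatment policy better than one that the Discussion calls a proof of principle.
- **Some details are not visible.** The flowchart (Fig. 4) is not shown, so the timing of the comparison spirometry is inferred from the 4-week delay. Case report forms may already record outside dental care. Neither changes the sentence in item {11d}.

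**Conclusion.** The concern holds. It rests on an explicit permission that works against the design, not on a detail the article left out. The direction is certain if the intervention works: the FVC difference shrinks by the factor 1 − c·f. The size is unknown. Under the article's central assumptions, with c up to 20%, the loss runs from about 2 percentage points of power (5% of controls, half effect) to about 17 points (20% of controls, full effect). Contamination in a 4-week window may well lie near the low end. The change is worth making because it is cheap and because a null result would otherwise be harder to interpret. The point does not threaten the validity of a positive result.

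**What to change.** Replace the sentence in item {11d} with a rule along these lines:

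- In both arms, elective professional tooth cleaning and CHX or other antiseptic mouth rinses outside the allocated schedule are deferred until after the spirometry that closes the comparison, about 4 weeks after the phase 2 baseline.
- Needed dental or medical care is never withheld.
- Any outside cleaning or antiseptic rinse is recorded at the existing visits.
- Participants who have such care stay in the analysis in the arm to which they were randomised.

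Recording antibiotic use would also help the microbiome outcome, but is optional.

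The cost is one or two sentences in the protocol and one question per visit. The only burden on participants is postponing elective cleaning and antiseptic rinses for about 4 weeks, a delay of the length that Trial design {8} already accepts for the intervention itself.

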#### Provisions for post-trial care {30}

The study protocol includes only established preventive dental interventions. Therefore, post-trial access to products or agents which are commercially non-available is not applicable for this trial.

### Outcomes {12}

The primary outcome is the pre- and post-bronchodilation lung function testing with the recording of the following clinical variables:Forced vital capacity (FVC)Forced expiratory volume in 1 s (FEV_1_)Forced expiratory flow at 25–75% of the pulmonary volume (FEF_25–75_)

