## Abstract

**Background:**

Periodontal disease and lung function impairment were found to be associated with low-grade systemic or local inflammation, and it might be that gingival/periodontal inflammation triggers lung function due to systemic inflammation or the transfer of oral bacteria or its components to the lung. A recent observational study in non-smoking subjects showed that lung volumes and flow rates were significantly reduced by 71–185 ml for severe gingivitis regardless of the adjustment for potential confounders. The result did not show any confounding by smoking, and the association between gingivitis and lower lung function was not modified by systemic inflammation. The designed interventional trial primarily aims to test the hypothesis that gingivitis reduction by optimized daily oral hygiene, professional tooth cleaning and antibacterial chlorhexidine (CHX)-containing mouth rinse improves lung function in terms of forced vital capacity (FVC) by at least 2%. The secondary objective will test the hypothesis that gingivitis reduction improves forced expiratory volume in 1 s (FEV1) and forced expiratory flow at 25–75% of the pulmonary volume (FEF25-75) by at least 2%. Furthermore, the influence of the oral microbiome will be taken into account.

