### Objectives {7}

The main objective is to test the hypothesis that gingivitis reduction via optimized daily oral hygiene and antibacterial chlorhexidine-containing (CHX) mouth rinsing improves lung function in terms of forced vital capacity (FVC), as an indicator of lung volume, by at least 2%. This allows interpreting the changes in lung function as direct or indirect consequences of changes in oral inflammation.

As a secondary objective, we test the hypothesis that gingivitis reduction by improved oral hygiene and CHX mouth rinsing improves forced expiratory volume in 1 s (FEV_1_) and forced expiratory flow rate at 25–75% of lung volume (FEF_25–75_), as indicators of airway obstruction, by at least 2%. Compared to the change in FVC, this will also allow to detect potential improvements regarding airway obstruction in terms of their ration FEV_1_/FVC. This is helpful for the interpretation of an improvement in lung function as a factor linked to a lower risk for obstructive airway disease.

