### Lung function testing by spirometry

Spirometry prior to bronchodilation will be performed in line with ATS/ERS recommendations [40]. Subjects will sit while wearing nose clips, and the EasyOne Worldspirometer (ndd, Zurich, Switzerland) will be used to obtain flow-volume curves. To obtain optimal flow-volume curves, the participants perform at least three, but no more than eight, manoeuvres under the guidance of specifically trained and experienced examiners. All tests will be visually inspected by experienced physicians according to the ATS/ERS acceptability criteria [40]. Spirometric indices will be taken from the manoeuvre with the largest sum of forced expiratory volume in 1 s (FEV_1_) and forced vital capacity (FVC). Further parameters evaluated will be the ratio of FEV_1_ and FVC (FEV_1_/FVC), and the mean flow rate between 25 and 75% of FVC (FEF_25–75_). Standardized *z*-scores of the lung function parameters FEV_1_, FVC, FEV_1_/FVC and FEF_25–75_ will be calculated based on the reference equations for spirometry from the Global Lung Initiative (GLI—http://www.ers-education.org/guidelines/global-lung-function-initiative.aspx, [48]. After completion of baseline spirometry, subjects will inhale bronchodilator medication according to the ATS/ERS recommendations [40]. Two puffs (each 100 µg) of salbutamol will be delivered into a spacer (volumatic) by a metered-dose inhaler, and the participant will be asked to take five slow and deep breaths over 5–10 s for optimal deposition. Spirometry will be repeated 15 min after salbutamol inhalation. This analysis uses post-bronchodilator lung function data. A positive response is defined as an increase by > 12% and > 200 ml in FEV_1_ and/or FVC post-bronchodilation compared to pre-bronchodilation, according to ATS/ERS standards [40].

Specific attention will be paid to the requirement to obtain very precise and reliable lung function data. In addition to strictly following ATS/ERS recommendations, we will reach the goal of high-quality lung function testing by experienced and well-trained study nurses, the additional visual control by a pulmonologist and the repetition of tests for each subject. There is long-standing, well-documented expertise on lung function assessment in the investigators involved in this study.

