### Biosampling and measurements of the microbiome

The secondary outcome is considered the bacterial composition. Both saliva and gingival fluid will be collected from the participants. Gingival fluid between the teeth will be collected with sterile paper points at 6 per-protocol predetermined sites in the lower jaw (mesial and distal at the “Ramfjord” teeth 41, 44 and 36) and 6 sites in the upper jaw (mesial and distal at the “Ramfjord” teeth 21, 24, 16). The samples will be frozen directly after collection, in separate vials for the upper and lower jaw samples. Saliva will be collected as well. Subjects are asked to chew for 1 min on a paraffin gum.

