However, this study has also some limitations. The major limitation is related to the uncertainty about the results, because of the high novelty and the innovative characteristics of this proposed study. Due to the high methodological experience of the study group, the strong focus of an interventional study and the strong design, we believe to provide a sound answer to the underlying research question regardless of whether we could prove the primary hypothesis. (8) Finally, this trial also might have clinical implications, although the effect size of lung function changes may seem small. The power calculation of the study is based on assumed changes of 2% for FEV_1_ and FEF_25–75_ during the time of the trial. According to the available data, this is a justified and realistic assumption of short-term changes in lung function due to the oral sanitation programme. This assumed change can be considered as a conservative estimate, since real effects are more likely to be higher than smaller. From a clinical perspective, a 2% improvement in lung function per se is certainly small, but one has to put this into a lifelong scenario, considering the natural decline of lung function over time. If the improvement is not a one-time event but, at least in part, a reduction in the annual rate of decline, the resulting difference in lung function after a number of years might very well matter, particularly.

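### Outcomes {12} makes FVC, FEV1 and FEF25-75, pre- and post-bronchodilator, the primary outcome, against FVC alone in the Objectives; the bronchodilator state and the variable behind the power calculation are also inconsistent

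*Protocol article*

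**What the plan says.** All places are in the protocol article.

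- **Objectives {7}, main objective:** the intervention "improves lung function in terms of forced vital capacity (FVC), as an indicator of lung volume, by at least 2" per cent. FVC is the only variable named.
- **Objectives {7}, next paragraph:** "As a secondary objective, we test the hypothesis that gingivitis reduction by improved oral hygiene and CHX mouth rinsing improves forced expiratory volume". The variables meant are FEV1 and FEF25-75. The Abstract gives the same ranking.
- **Outcomes {12}:** "The primary outcome is the pre- and post-bronchodilation lung function testing with the recording of the following clinical variables", followed by FVC, FEV1 and FEF25-75 with no order among them.
- **Lung function testing by spirometry:** "This analysis uses post-bronchodilator lung function data".
- **Biosampling and measurements of the microbiome:** "The secondary outcome is considered the bacterial composition".
- **Sample size {14}:** one two-sided comparison of two mean changes at alpha 0.05 and 90% power. The units are generic and no lung function variable is named.
- **Discussion:** "The power calculation of the study is based on assumed changes of 2% for FEV_1_ and FEF_25–75_ during the time of the trial". FVC is not mentioned there.

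**The concern.** The primary outcome fixes which result answers the trial's question. Objectives {7} points to FVC. Outcomes {12} points to three variables in two bronchodilator states. The microbiome section fits {12} rather than the Objectives, because it leaves FEV1 and FEF25-75 no place among the secondary outcomes. That makes {12} hard to dismiss as a loose list. The Discussion sentence then links the power calculation to the two variables that the Objectives call secondary.

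At stake is whether the trial has one confirmatory answer. Someone following {12} could report a significant FEV1 or FEF25-75, before or after salbutamol, as the primary result. Someone following the Objectives would call the same finding secondary. The sample size section allots the whole 5% to a single comparison, so it supports only one such result.

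**Working it through.** **1. The plan's own sample size.** Inputs from Sample size {14}: difference 2 − 1 = 1; variance per assessment 1.5, so variance of a change 3 and SD √3, rounded in the text to about 1.7; two-sided alpha 0.05; power 90%.

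n per group = 2 × SD² × (1.960 + 1.282)² / 1²

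- SD 1.7: 2 × 2.89 × 10.507 = 60.7, so 61. This matches the stated 61.
- SD √3: 2 × 3 × 10.507 = 63.04, so 64. The gap comes from rounding the SD and is not the point here.

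The calculation covers one test at the full 5%. At 60 per group its power is 88.5% with SD √3 and about 90% with SD 1.7.

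**2. How many primary results the text allows.**

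| Sections read together | Candidate primary results |
|---|---|
| Outcomes {12} alone | 3 variables × 2 bronchodilator states = 6 |
| Outcomes {12} with the spirometry section | 3 variables, post-bronchodilator = 3 |
| Objectives {7} with the spirometry section | post-bronchodilator FVC = 1 |

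Only the last row agrees with a calculation for one comparison at 5%.

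**3. Error rate if any one significant result counted as success.** This success rule is an assumption. Each test is taken at two-sided 5% without adjustment. The documents give no correlations, so a common correlation is assumed and varied. Under independence the rate is 1 − 0.95^k. The other rows are simulated as the share of draws with at least one |z| above 1.96.

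| Assumed correlation | 3 tests | 6 tests |
|---|---|---|
| 0 (upper bound) | 14.3% | 26.5% |
| 0.5 | 12.5% | 20.7% |
| 0.7 | 10.9% | 16.4% |
| 0.9 | 8.4% | 10.9% |

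Every entry is above 5%.

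**4. What keeping several primaries would cost.** With Bonferroni adjustment, SD √3 and a normal approximation, the standardised difference at 60 per group is 1 / (√3 × √(2/60)) = 3.162.

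- 3 tests, alpha 0.05/3 = 0.0167: power per test Φ(3.162 − 2.394) = 77.9%. For 90%, n = 6 × (2.394 + 1.282)², giving 82 per group.
- 6 tests, alpha 0.05/6 = 0.0083: power per test Φ(3.162 − 2.638) = 70.0%. For 90%, n = 6 × (2.638 + 1.282)², giving 93 per group.

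The planned size of about 60 per group therefore suits a single primary outcome.

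**The case against.** The other side has a good case on several points.

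- **The hierarchy is already stated.** The lung function hypotheses appear in the Abstract and Objectives, where they are ranked. Outcomes {12} can be read as a list of what is recorded. This reading is reasonable, but {12} still labels all three variables primary and the microbiome section still gives a different secondary outcome. Even on this reading those sections need correcting.
- **The spirometry sentence is not a rival outcome definition.** A reader might count three incompatible definitions of the primary outcome. The documents do not support that count. The post-bronchodilator sentence describes the data analysed and agrees with the Objectives; together they give post-bronchodilator FVC. It conflicts only with the pre- and post-bronchodilation wording in {12}.
- **Six planned tests are not stated.** A reader might infer that the trial will run six primary tests with a 26% false-positive rate. Six is the most that {12} allows, and no section says that any one significant variable would count as success. Independence is not credible for indices taken from the same breathing manoeuvres in the same people, so 26.5% is only a ceiling.
- **Multiplicity control may be in the analysis plan.** The article controls the false discovery rate for the microbiome only. A procedure for lung function variables is commonly left to the analysis plan, which is not shown, so its absence is not a fault. The fault is that the article ranks the variables inconsistently, and an analysis plan would have to contradict at least one section to resolve that.
- **The Discussion does not exclude FVC from the power calculation.** It names FEV1 and FEF25-75 and is silent on FVC. The calculation in {14} is unit-free and belongs to no variable. What stands is that the only sentence naming variables leaves out the main one.

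**Conclusion.** The contradiction is in the current text and holds whatever the analysis plan says. Outcomes {12} and the microbiome section do not match the ranking in the Abstract and Objectives {7}. The bronchodilator state differs between {12} and the spirometry section. Sample size {14} names no outcome, and the Discussion names only the two variables that the Objectives call secondary.

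The effect on error is conditional. It requires that any one significant result be taken as success, and it depends on correlations that the documents do not give. Over 0.9 down to 0.5, the unadjusted error is 8.4% to 12.5% for three tests and 10.9% to 20.7% for six, against a nominal 5%. If the Objectives and the spirometry sentence govern, there is one primary test and no inflation. The text should say so in every place.

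**What to change.** - **Outcomes {12}:** state one primary outcome, the between-arm difference in pre-post change in post-bronchodilator FVC over the phase 2 comparison period. Take the time point from Fig. 4, which is not shown in the text at hand. This uses the plan's own choices in Objectives {7} and the spirometry section.
- **Secondary outcomes:** list FEV1, FEF25-75 and the pre-bronchodilator values, alongside bacterial composition, and reword the microbiome section to match. How these are tested can be left to the analysis plan.
- **Sample size {14}:** name FVC as the outcome to which the effects and variances refer.
- **Discussion:** align the sentence on the power calculation with {14}.

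If several primary variables are really wanted, state the success rule and the multiplicity procedure, and recalculate the sample size.

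The single-outcome fix costs wording only. FEV1 and FEF25-75 lose primary status. The Trial status section describes recruitment as still planned, so at the time of the document the change could be made before any outcome data existed.
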